#### **Suspected Unexpected Serious Adverse Reaction (SUSAR)**

A serious adverse reaction by its nature, incidence, severity, or outcome is unanticipated and not identified in the intervention’s instructions for use or safety information are classified as a SUSAR.

Fatal or life-threatening Australian SUSAR reports are reported to the Coordinating Principal Investigator, the sponsor's delegate and the approving HREC within 7 calendar days after being made aware of the case follow up information reported within a further 8 calendar days.

All other Australian SUSAR reports are to be reported to the Coordinating Principal Investigator, the sponsor's delegate and the approving HREC within 15 calendar days after being made aware of the case follow up information reported within a further 8 calendar days. SUSAR reports must be recorded in the [UNSW Safety Monitoring Register Template](https://research.unsw.edu.au/document/UNSW%20Safety%20Monitoring%20Register%20Template.xlsx).

Participants may be withdrawn from the study if they experience a serious adverse event that is attributable to a study intervention or procedure; or means they can no longer participate in the study. The team clinical psychologist will follow-up with subjects withdrawn due to experiencing a serious adverse event that was attributable to the study intervention or procedure. These participants will be contacted via email 1-week after they are withdrawn from the trial to provide a list of crisis contact numbers for support. In this email, participants will also be asked to respond to the email (by clicking ‘reply’) if they would like to receive a phone call from the team clinical psychologist during business hours (9:00 to 17:00 AEST) within the next 3 days. SAE reports are classified following the safety assessment flowchart and are assessed by Sponsors Independent Medical specified in section 2 of the protocol. The Sponsors Independent Medical cannot delegate this responsibility to other research personnel. SAE reports are reported to the Coordinating Principal Investigator within 24-hours for multicentre clinical trials. SAR reports must be recorded in the [UNSW Safety Monitoring Register Template](https://research.unsw.edu.au/document/UNSW%20Safety%20Monitoring%20Register%20Template.xlsx).

Significant Safety Issue (SSI)

A safety issue that could adversely affect participants' safety or materially impact the trial's continued ethical acceptability or conduct. The Human Research Ethics Committee and Sponsor's Delegate must be notified of all significant safety issues within 15 calendar days of the sponsor instigating or being made aware of the issue**.** SSI reports must be recorded in the [UNSW Safety Monitoring Register Template](https://research.unsw.edu.au/document/UNSW%20Safety%20Monitoring%20Register%20Template.xlsx).

Register of Clinical Trial Safety Monitoring Reports

A register of all event reports assessed and classified is to be retained by the Coordinating Principal Investigator and reported to the trial sponsor annually and the HREC if required.

Reporting of Clinical Trial Safety Monitoring Reports

Single case reports of Adverse Events Adverse Reactions, Serious Adverse Events (SAEs), Serious Adverse Reactions (SARs), reports do not need to be reported to the UNSW Sponsor's Delegate or the HREC. All single case reports must be recorded in a safety monitoring register and are reported to the UNSW Sponsor's Delegate annually.

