## **Withdrawal of Consent or Participant**

Participants may be withdrawn from the study if:

- They experience a serious adverse event that:
  - is attributable to a study intervention or procedure; or
  - means they can no longer participate in the study; or
- They withdraw consent to take part.
- We will not be replacing participants that are withdrawn from the study.

The team clinical psychologist will follow-up with subjects withdrawn due to experiencing a serious adverse event that was attributable to the study intervention or procedure. These participants will be contacted via email within 72 hours of withdrawing from the trial with a list of crisis contact numbers for support. In this email, participants will also be asked to respond to the email (by clicking ‘reply’) if they would like to receive a phone call from the team clinical psychologist during business hours (9:00 to 17:00 AEST). If they say yes, they will be contacted within the following 72 hours.

Participants can self-withdraw at any time by submitting to the study team the UNSW standard withdrawal form appended to the Participant Information Statement. No mechanisms for automated withdrawal (e.g. via the study app) will be provided. To ensure that data belonging to a participant who withdraws can be uniquely identified, their mobile number and email address will be solicited on the withdrawal of participation form. Excluding self-withdrawals, the decision to withdraw a participant will be made by the Principal Investigator.

Handling of participant data after withdrawal will depend on when a participant decided to withdraw from the study. Participants will have their data removed from the study if they withdraw or are withdrawn prior to completion of the baseline assessment. Reflecting the intention-to-treat principles informing the planned analyses of the trial, data from participants who withdraw after this point will not be discarded.

Those who complete baseline and are randomly allocated but then complete no subsequent surveys will not be treated as withdrawal but handled as missing data unless the specifically request to have their data withdrawn. Responsibility for confirming successful withdrawal of data will be assigned in the Delegations Log.

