Non-identifiable data about withdrawals enabling aggregate reporting (e.g. counts by intervention assignment) will be retained in the Withdrawals Log which is part of the Safety Monitoring Register (see Appendix B). In addition, any participant withdrawal linked to an adverse event will be recorded to enable reporting of safety-related statistics. Participants who withdraw from the study will not be replaced and will not be followed up except per adverse event follow-up, if applicable (see Risk Management Protocol, Appendix G).

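### The protocol gives two incompatible deadlines, 72 hours and one week, for the crisis-support email to participants withdrawn after a study-attributable serious adverse event

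*Protocol*

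**What the plan says.** Two sections of the protocol set out what happens after a participant is withdrawn following a serious adverse event. Both say that the team clinical psychologist follows up "subjects withdrawn due to experiencing a serious adverse event that was attributable to the study intervention or procedure".

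- **Withdrawal of Consent or Participant:** "These participants will be contacted via email within 72 hours of withdrawing from the trial with a list of crisis contact numbers for support". The participant may reply to ask for a call from the psychologist, and then "If they say yes, they will be contacted within the following 72 hours".
- **Suspected Unexpected Serious Adverse Reaction (SUSAR):** "These participants will be contacted via email 1-week after they are withdrawn from the trial", again with the crisis numbers. The participant may reply in the same way to ask for a call "during business hours (9:00 to 17:00 AEST) within the next 3 days".

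The withdrawal section adds that participants who leave the study "will not be followed up except per adverse event follow-up, if applicable", and refers to the Risk Management Protocol for that follow-up.

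**The concern.** The same email to the same people has two send dates. Staff who work from the SUSAR section as written will breach the withdrawal section every time. Staff who work from the withdrawal section will never send the email when the SUSAR section says it goes out.

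Timeliness is the purpose of this step. The trial enrols people aged 17 to 24 with suicidal thoughts in the past 30 days. Apart from a death, the serious adverse events the protocol defines are a suicide attempt or self-injury that needed medical treatment. Those withdrawn under this rule have had such an event, and it has been attributed to the study. The protocol also counts any departure from its requirements as at least a deviation, so the conflict makes avoidable deviations likely whichever sentence staff follow.

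**Working it through.** No statistical formula applies. The check sets the two rules side by side, converts units, and looks for anything elsewhere in the protocol that reconciles them.

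**1. Is it the same email?**

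| Element | Withdrawal of Consent or Participant | SUSAR section |
|---|---|---|
| Recipients | Withdrawn for a serious adverse event attributed to intervention or procedure | Same |
| Content | Crisis contact numbers | Same |
| Offer | Psychologist call in business hours, requested by reply | Same |
| Email timing | Within 72 hours of withdrawal | 1 week after withdrawal |
| Call timing | Within 72 hours of a yes | Within 3 days |

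Only the email timing differs. The call windows have the same length, because 72 h / 24 = 3 days.

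**2. Size of the email conflict.**

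- Withdrawal section: at most 72 h, i.e. day 3.
- SUSAR section: 7 × 24 = 168 h, i.e. day 7.
- Gap: 168 − 72 = 96 h = 4 days at the least. It is larger if the email under the first rule goes out before its limit.

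**3. Consequence for the call, assuming an immediate reply.**

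- Withdrawal section: latest day 3 + 3 = day 6.
- SUSAR section: earliest day 7, latest day 7 + 3 = day 10.
- The windows do not overlap, and the latest dates differ by 10 − 6 = 4 days.

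This follows entirely from the email date and is not a second discrepancy. A slower reply moves these dates.

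**4. Does anything else settle the timing?**

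- *Two separate emails.* Neither section mentions a first or a second message, and recipients, content and offer coincide.
- *A rule for SUSARs only.* The paragraph stands under the SUSAR heading, but it restates the general withdrawal rule and is not limited to unexpected reactions.
- *Risk Management Protocol.* It times the response to survey flags and gives no timing for withdrawn participants.
- *DSMB charter, Trial Stopping Guidelines.* This refers to a 48-hour contact period for participants flagged as at risk. The trigger is the flag, not withdrawal, so it does not choose between 72 hours and one week.
- *Superseded text.* Both sentences are complete and stand in the current protocol.

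**The case against.** The strongest reply is that little harm follows. Under the Flagging procedure in the Risk Management Protocol, a participant who reports an attempt, or self-injury needing medical care, in a survey is sent an automated email. That email carries the crisis contacts and also offers a psychologist call within 3 working days. Every participant also sees the same contacts on finishing each survey. For events reported by survey, both elements of the withdrawal email have therefore already been offered, and a call on days 7 to 10 would not be the first one available. The affected group is also small: withdrawn, after a serious event, judged attributable. The protocol gives no expected number, and no analysis depends on it.

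Most of this stands, and it limits the weight of the point. It does not remove the conflict. The automated alert is triggered by survey answers, whereas the Safety Analyses section of the DSMB charter also recognises attempts and self-injury that participants report ad hoc to the study email address. No automated alert is described for that route, so the withdrawal email may be the first crisis information the protocol schedules for those participants.

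A second reply is that 72 hours should not be treated as the protective standard when the charter mentions 48 hours for flagged participants. That is fair as a prompt to check the two rules against each other. It gives no support to one week.

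**Conclusion.** The contradiction is real. One email cannot go out both within 3 days of withdrawal and 7 days after it, and nothing else in the protocol says which applies. The email gap of at least 4 days needs no assumption beyond the wording. The comparison of calls (by day 6 against day 7 to day 10) assumes an immediate reply.

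This is an internal inconsistency in a safety procedure. It should be corrected because it concerns a high-risk group and the correction is nearly free. It has no bearing on randomisation, endpoints, sample size, error rates or the efficacy analysis. For events reported by survey it affects a second layer of follow-up; for events reported ad hoc by email it may affect the first.

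**What to change.** In the SUSAR section, replace the one-week timing of the email with the limit of 72 hours from withdrawal that already stands in Withdrawal of Consent or Participant. Use the withdrawal section's call timing, 72 hours from the participant's yes, in both places. This keeps the more protective of the two deadlines.

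While editing, the sponsor should confirm whether the 48-hour contact period in the charter's Trial Stopping Guidelines is meant to reach withdrawn participants, and say so either way.

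The cost is about a sentence of protocol wording, with no change to design, data collection or analysis.

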# **Non-compliance, Protocol Deviation and Serious Breaches of Good Clinical Practice**

## **Protocol Deviation**

A protocol deviation is defined as any breach, divergence or departure from the requirements of Good Clinical Practice, the clinical trial protocol, the clinical trial standard operating procedures, or the human ethics approval that does not have a significant impact on the continued safety or rights of participants or the reliability and robustness of the data generated in the research or clinical trial. Protocol deviations are events that do not occur persistently or systematically and do not potentially result in participant harms. Examples of protocol deviations include but are not limited to:

- Deviations because of participant adherence to the protocol, including rescheduled study visits, participants refusal to complete scheduled research activities
- The completion of consent forms, safety monitoring report, case report forms or data collection tools in a manner that is not consistent with the protocol instructions or failure to make reports within the required reporting timeframes.
- Use of an unapproved version of the participant information statement or recruitment of participants using unapproved recruitment procedures.
- Inclusion of a participant that does not meet the inclusion criteria.
- An urgent safety measure must be taken to eliminate an immediate hazard to a participant's health or safety.

##

## **Serious Breach of Good Clinical Practice**

A serious breach is defined as a breach of Good Clinical Practice, the clinical trial protocol, the clinical trial standard operating procedures, or the human ethics approval that is likely to affect to a significant degree the safety or rights of participants or the reliability and robustness of the data generated in the clinical trial. Examples of serious breaches include but are not limited to:

- Persistent or systematic non-compliance with the instructions for completing consent forms, safety monitoring forms, case report forms or data collection tools that result in continued missed or incomplete data collection.
- Failure to record or report adverse events, serious adverse events, suspected unexpected serious adverse reactions, significant safety issues where urgent safety measures were implemented.
- Failure to conduct clinical trial procedures following the clinical trial delegation log.
- Widespread and uncontrolled use of protocol waivers affecting eligibility criteria, which leads to harm to trial subjects.
- Failure to report investigational medical product or device defects to the clinical trial sponsor or any relevant regulatory body.
- Failure to conduct research following the issued approvals, permits or licences by required laws, regulations, disciplinary standards, and UNSW policies relating to the responsible or safe conduct of research.
- Concealing or facilitating breaches (or potential breaches) of the Research Code by others.
- Researching without the requisite approvals, permits or licences required by laws, regulations, disciplinary standards, and UNSW policies related to the responsible or safe conduct of research.
- Failure to conduct research as approved by an ethics review body where that conduct leads to (or has the potential to) results in participant harms.
- Researching without ethics approval as required by the National Statement on Ethical Conduct in Human Research where that conduct leads to (or has the potential to) result in participant harms.
- Any breaches as outlined in the UNSW Research Misconduct Procedure or the Australian Code for responsible conduct of research that leads to (or can potentially) result in participant harms.

## **Reporting Protocol Deviations**

- Protocol deviations occurring at a site must be documented in site files and reported by the principal site investigator to the Coordinating Principal Investigator.
- The Coordinating Principal Investigator must review the protocol deviation and the clinical trial protocol to establish the corrective actions and preventative steps to prevent the deviation from reoccurring.
- The protocol deviation and corrective action plan must be reported to the UNSW Sponsor's Delegate by the Coordinating Principal Investigator or Coordinating Research Team using the protocol deviation report form.

## **Reporting of a Serious Breach**

- The Principal Investigator must report a serious breach occurring at a participating site to the Coordinating Principal Investigator within a specified timeframe.
- The Coordinating Principal Investigator must review the serious breach, along with the clinical trial protocol, to develop a Corrective and Preventive Action (CAPA, Appendix L) that defines the steps to prevent the serious breach from reoccurring.
- The serious breach report and the CAPA must be provided to the approving HREC, and the UNSW sponsors delegate for review and approval.

# **Review of a Protocol Deviation and a Serious Breach**

- The UNSW Sponsor's Delegate will review reports to establish whether the event meets the definition of a protocol deviation or serious breach, establish whether the proposed CAPA is appropriate and establish whether there is or will be ongoing impact reliability and robustness of the data generated.
- The UNSW Sponsor's Delegate will seek advice from the approving HREC on the corrective and preventive actions.
- Protocol deviation or serious breach reports where a UNSW researcher, staff or student is responsible for the protocol deviation or the serious breach will be reviewed as per the [UNSW Research Misconduct Procedure](https://www.gs.unsw.edu.au/policy/documents/researchmisconductproc.pdf) to establish a breach of the [UNSW Research Code of Conduct](https://www.gs.unsw.edu.au/policy/documents/researchcode.pdf) has occurred.
- Protocol deviation or serious breach reports where the UNSW Sponsor's Delegate determines that site personnel are responsible for a protocol deviation or the serious breach will be referred onto their responsible institution for review under their Research Misconduct procedures to establish whether a breach of the [Australian Research Code for the Responsible Conduct of Research](https://www.nhmrc.gov.au/about-us/publications/australian-code-responsible-conduct-research-2018) has occurred.

# **Statistical analytical plan**

Mixed models repeated measures (MMRM) analyses, with maximum likelihood estimation and an appropriate covariance structure, will be used to evaluate longitudinal changes in suicidal ideation and secondary mental health outcomes between the LifeBuoy and attentional control arms. Where required, generalised linear mixed models with an appropriate link function will be used for the analysis of categorial variables. The primary outcome is severity of suicidal ideation, as measured by the Suicidal Ideation Attributes Scale [SIDAS], over time (baseline T0, 30-days T1, 60-days T2, and 120-days T3). The mixed model approach incorporates all available data, including participants with missing follow-up data points, under the missing-at-random assumption. Analyses will therefore accord with the intention-to-treat principle.

Descriptive statistics will be used to examine the level of engagement in three arms (LifeBuoy, LifeBuoy + engagement, and control). Engagement will be measured by the number of modules completed by participants. Participant module access and module completion will be automatically collected via the app.

Qualitative feedback on users’ perceived acceptability of the LifeBuoy app and engagement strategy will be examined through semi-structured interviews with a subset of participants (n=30 in total) and questionnaires in the survey. The interview data will be analysed using thematic analysis. An inductive approach, independent of a theoretical confirmative method will be used to identify and group themes. The researchers will then refine the themes and determine the final coding framework. Discrepancies will be resolved by a third researcher to ensure reliability of the process.

Any deviation from the original statistical plan will be described and justified in the final report.

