Efficacy of the engagement strategy: the other primary objective is to explore whether participants who receive LifeBuoy + a digital engagement strategy report higher rates of app usage (measured in terms of the number of modules completed, number of app logins, and total time spent on the app) relative to the LifeBuoy-only condition. This trial will answer important questions about whether, and what, digital strategies improve user engagement, addressing key knowledge gaps in the digital health field. Previous research has shown that technology-based strategies can potentially improve user engagement [14]. However, a plausible reason why many such strategies fail is because they do not sufficiently address the needs of users and are thus not well-received [15]. Moreover, few studies have examined the efficacy of social media (e.g., Instagram) and blog posts in promoting greater engagement with DMHIs. More specifically, we will examine the efficacy of a digital engagement strategy – designed to optimise use of the LifeBuoy app – on app adherence (measured in the following ways: number of modules / activities / exercises completed; number and frequency of app log-ins; total time spent on the app) by comparing 2-arms: LifeBuoy + engagement strategy versus LifeBuoy-only at 0-days (baseline, T0), 30-days (T1), 60-days (T2), and 120-days (T3).

Secondary outcomes

1. To determine whether the LifeBuoy app reduces incidents of suicide attempt and non-suicidal self injury relative to the control condition at T1, T2, and T3.
2. To assess whether the LifeBuoy app reduces depression and anxiety symptoms relative to the control condition at T1, T2, and T3.
3. To examine whether the LifeBuoy app + engagement condition reduces suicidal ideation relative to the LifeBuoy-only condition at T1, T2, and T3.

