# **Trial Design**

This parallel design randomised controlled trial will involve three arms to answer the main objectives outlined in Section 4: 1) attentional control, 2) LifeBuoy only, and 3) LifeBuoy + engagement strategy. Participants will be followed up over four time-points: 0-days (baseline, T0), (0 days), 1-month (30- days (T1), 2-months (60- days (T2), and 4-months (120-days (T3).

The primary endpoint is change in suicidal ideation at T1 (day-30) relative to T0 (baseline, day-0).

The secondary endpoint is adherence to the LifeBuoy app across time, defined as the number of modules completed by participants at the T1, T2, and T3 post-baseline time-points. Participant module access and module completion data will be automatically collected via the LifeBuoy app.

The following flow chart (Figure 1) describes how an individual participant will progress through the phases of the research process:

[figure not shown]

*Figure 1: Study Process Flow*

Randomisation to treatment arms will occur on a 1:1:1 ratio using a block design using an automated web-based platform tailored for this project. All study assessments will be via electronic self-report. There are no outcome assessors.

Participants will have until the end of the 120-day period to access the apps. They will be prospectively followed up over four time-points: 0-days (baseline, T0), (0 days), 30- days (T1), 60- days (T2), and 120-days post baseline (T3). After completion of the T1 assessment, participants from the LifeBuoy (n=20) and LifeBuoy + engagement strategy (n=20) conditions will be invited to participate in a qualitative interview about the acceptability of the app and engagement strategy (n=40 in total). Participants will be recruited on a first-in first-served basis, and interviews will be conducted within 1-month of completing the T1 assessment to minimise memory failure relating to the engagement strategies.

The discontinuation criteria for individual participants will include if they experience a serious adverse event (Section 9.6 details withdrawal procedures).

The following accountability procedures for the intervention and control apps will apply:

- Software version control ensuring only approved/tested version of each intervention is used in the trial.

Randomization codes will be generated and retained automatically by the Black Dog Institute’s research engine.

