# **Sample Size**

The plan is to enrol 669 subjects to this trial. Sample size calculations were based on the primary aims. For Aim 1, to detect an expected minimum effect size of d=0.45 between the LifeBuoy intervention and the control condition on the primary measure of suicidal ideation (SIDAS), determined from the prior LifeBuoy trial (paper in review), with α = 0.01, power = 0.95, and assuming a 0.50 correlation between repeated measures, 112 subjects are needed in each condition. As a three-arm trial, with a 1:1:1 allocation, this means N=336 subjects are required to detect this effect. In addition, assuming an attrition rate of 25% in each group at our 30-day assessment based on the previous trial of LifeBuoy, 450 participants are needed (150 in each arm, rounded up). This sample size is sufficient to detect the expected effects associated with primary aim 1. For Aim 2, our recent systematic review of the engagement literature yielded three studies which were similar in design and population to our study34-36. The effect sizes in these studies varied from d = .04 to .53 reflecting a difference in user engagement when comparing a digital intervention only and the same digital intervention with an engagement strategy. Given the small number of studies, there is insufficient information to assume that effect sizes are normally distributed. Thus, the median effect size among the 3 studies (d = .38) was used as a benchmark. To detect an effect size of d=0.38 for primary aim 2 (alpha 0.01, power 0.95, assuming a 0.50 correlation between repeated measures, and 25% attrition), 223 participants are needed in each arm (rounded up). With a 1:1:1 allocation, this means N=669 subjects are required. Therefore, the larger sample size of 669 participants will be chosen to meet requirements of both primary aims. Qualitative interviews with 40 young people from the LifeBuoy and LifeBuoy + engagement group (minimum of 20 participants from the latter) will be recruited at the 30-day assessment time point, in which they will be asked whether they are interested to take part in an interview about their experience of the app and engagement strategy. This sample size will be large enough to reach saturation of qualitative themes.

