Participants will have access to the app - to complete seven modules - until the end of the 120 day trial period. Each module will take approximately between five to ten minutes to complete. The user will be directed to each module linearly and unlocking a new module will require completion of the previous one (this also is the gamification of the app, as island ‘light up’ or become technicolour when complete). Once modules are unlocked, participants can re-access them at any time.

In addition to the LifeBuoy app, this study is seeking to trial a multicomponent digital engagement strategy aimed at increasing compliance with the LifeBuoy app. The engagement strategy will be comprised of 3 core components:

1. An Instagram account that will deliver brief, visual content that aligns to the strategies and educational information within the app itself.
2. A clinician-written blog that will provide a platform to deliver in-depth therapeutic information and advice for maintaining mental health.
3. Emails: weekly emails will be sent to participants with links to strategies 1 and 2, to remind them to visit them and in addition, the emails will suggest to participants what module within the app they might like to visit/explore that week and strategies for getting the most out of it.

The decision to leverage these specific platforms was derived from a bottom-up approach, where we have spent almost 18 months gathering information and perspectives from young people with a lived experience of suicide. The sources of data include: qualitative interview feedback from participants in the first LifeBuoy trial (HC190764); (ii) data from a broad online survey of 260 mental health app users in Australia (HC200616) (iii) and input from a youth lived experience project advisory group (HC210038). The content and design for the Instagram and blog posts is being developed in consultation with the youth lived experience project advisory group, all of whom were participants in the first LifeBuoy trial.

To deliver on the engagement strategy, Instagram posts will be uploaded at least once a week throughout the duration of the study, up till 30 days after recruitment of the final study participant. The Instagram account will be public, with comments disabled, as public access allows users to view content anonymously (otherwise they will need to register to view the account, which may be perceived as a barrier to engagement).

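### The engagement comparison raises the sample size from 450 to 669, but the only analysis the plan names for engagement is descriptive, across three arms

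*Protocol*

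**What the plan says.** Four sections of the protocol bear on the engagement aim.

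- **Trial Objectives and Purpose** gives it primary status: "the other primary objective is to explore whether participants who receive LifeBuoy + a digital engagement strategy report higher rates of app usage". Usage is measured by modules (or activities and exercises), log-ins and total time in the app. The contrast is fixed as two arms: "by comparing 2-arms: LifeBuoy + engagement strategy versus LifeBuoy-only at 0-days (baseline, T0), 30-days (T1), 60-days (T2), and 120-days (T3").
- **Sample Size** treats it as a hypothesis test: "To detect an effect size of d=0.38 for primary aim 2", with "alpha 0.01, power 0.95, assuming a 0.50 correlation between repeated measures, and 25% attrition". The result is 223 per arm. Aim 1 is stated to need 450 in total, and the section concludes that "the larger sample size of 669 participants will be chosen to meet requirements of both primary aims".
- **Trial Design** gives it a different status and a single measure: "The secondary endpoint is adherence to the LifeBuoy app across time, defined as the number of modules completed by participants", at T1, T2 and T3.
- **Statistical analytical plan** applies the mixed model to suicidal ideation and secondary mental health outcomes, LifeBuoy against control. It reserves generalised linear mixed models for categorical variables where required. For engagement it says: "Descriptive statistics will be used to examine the level of engagement in three arms (LifeBuoy, LifeBuoy + engagement, and control"). It adds that engagement is measured by modules completed.

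On the duration of the strategy, Trial Intervention says that Instagram posts continue "up till 30 days after recruitment of the final study participant", and gives the same limit for blog articles. Types of Safety and Monitoring instead places the end of updates at the close of data collection.

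**The concern.** A comparison sized at alpha 0.01 and 95% power is confirmatory. One expects the analysis section to give it a contrast, a model, an alpha and an interval. Here that section assigns it a description across three arms, one of which (control) has no part in the contrast. This is a positive statement that does not match the sizing. It is not a detail left open for a separate statistical analysis plan. The same section also says that any departure from the original statistical plan must be described and justified, so a test added later would itself be a departure.

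Two things are at stake. If the text is followed, the aim that justifies the larger sample yields no between-arm test or interval. If a test is chosen after the data are seen, three measures and three post-baseline time points are on offer, and nothing in the text says which is the primary one.

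**Working it through.** **Inputs (all from Sample Size unless noted).** Aim 1: d = 0.45, alpha 0.01, power 0.95, correlation 0.50, attrition 25%; stated 112 per arm, 150 after attrition, 450 in total. Aim 2: d = 0.38 with the same alpha, power, correlation and attrition; stated 223 per arm, 669 in total. Sidedness and the number of repeated measures m are not stated. I assumed a two-sided test and tried m = 1 to 4.

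**Step 1. Reproduce the plan's figures.** For a two-group repeated-measures between-arm F test, f = d/2 and the noncentrality is λ = N f² m / (1 + (m − 1)ρ), with N the total in the two arms.

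- Aim 2, m = 3 (T1 to T3), 167 per arm: λ = 334 × 0.19² × 3/2 = 18.1, power 95.1%. Then 167/0.75 = 222.7, rounded up to 223, and 3 × 223 = 669. This matches exactly.
- Aim 1, m = 4 (T0 to T3), 112 per arm: λ = 224 × 0.225² × 4/2.5 = 18.1, which reaches 95%. Then 112/0.75 = 149.3, rounded up to 150, and 3 × 150 = 450. This matches exactly.
- For Aim 2 other values of m do not match: after attrition, m = 1 gives 332 per arm, m = 2 gives 250 and m = 4 gives 208. A one-sided baseline-adjusted formula (variance factor 1 − ρ²) gives 220, which is close but not exact.

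So 669 is what a powered two-arm test over three post-baseline measures requires.

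**Step 2. What Aim 2 adds.** 669 − 450 = 219 participants, or 219/669 = 33% of the total, which is 73 per arm.

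**Step 3. Error if the test is chosen later, each at 0.01.**

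- Three measures × three time points: 1 − 0.99⁹ = 0.086.
- Modules only, three time points: 1 − 0.99³ = 0.030.

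Both assume independent tests.

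**Step 4. Power of the two candidate tests (d = 0.38, two-sided alpha 0.01).**

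| Test | 167 per arm | 223 per arm |
|---|---|---|
| Repeated measures, T1 to T3, ρ = 0.50 | 95.1% | 99.0% |
| Single measure, modules by T1 | 81% | 92% |

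For the single measure, the normal approximation at 223 per arm is Φ(0.38 × √(223/2) − 2.576) = Φ(1.437) = 92.5%; the noncentral t gives 92.2%. At 167 per arm the two give 81.5% and 81.0%. Holding 95% with a single measure needs about 249 per arm with no loss.

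The repeated-measures figures depend on the 0.50 correlation. Modules completed by T1, T2 and T3 is a cumulative count, so its correlation may be higher. As ρ approaches 1 the factor m/(1 + (m − 1)ρ) falls to 3/3 = 1, and power falls to the single-measure row.

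**The case against.** The strongest reply is that this is loose drafting. The objective speaks of exploring, the analysis section does not say that engagement will be described and nothing more, and a separate analysis plan may name the two-arm model. It stands that exploratory status is a legitimate choice. But then the primary label and the 669 cannot rest on a test at alpha 0.01 with 95% power, so one side or the other has to change.

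Several stronger readings are tempting, and the protocol does not support them.

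- *The trial cannot test the engagement aim.* The arms are randomised, usage is logged automatically and the two-arm contrast is stated in the objectives. What is missing is a named test.
- *No estimate will be produced.* Descriptive statistics by arm still give arm-level estimates. The gap is the between-arm test and its interval.
- *The 219 extra participants serve only this aim.* They also enter the planned mixed model for suicidal ideation and the mental health outcomes, and the 73 extra controls lie outside the engagement contrast. Aim 2 justifies the excess but is not its only use.
- *A false-positive rate near 37%.* That is 1 − 0.95⁹, and the protocol sets 0.01 for this aim, not 0.05. Even the 8.6% is towards the upper end, because modules, log-ins and time recorded in the same users are probably positively correlated.
- *The strategy ends before T2 and T3.* The stated limit covers new posts and articles. No end date is given for the weekly emails, and the number of participants affected depends on an accrual period that is not stated.

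**Conclusion.** The mismatch is real and should be fixed before the data are seen. The engagement comparison is a primary objective, is powered as a test and accounts for the rise from 450 to 669. The analysis section nevertheless gives it descriptive statistics in three arms, and Trial Design calls it secondary. As written, it gets no confirmatory comparison. Leaving the choice of test open risks a family-wise error of up to about 8.6% across nine candidate tests at 0.01, or about 3% for modules alone, both under independence.

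The reading of the sample size as a two-sided test with three measures is inferred from an exact match, since the protocol states neither. All power figures use normal theory at d = 0.38. They approximate, and do not replace, the power of a model for a bounded count of 0 to 7 modules.

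**What to change.** In the Statistical analytical plan, replace the descriptive sentence with one prespecified test: modules completed, LifeBuoy plus engagement versus LifeBuoy-only, all randomised participants of those two arms (2 × 223 = 446), two-sided alpha 0.01, with effect estimate and confidence interval, from a model suited to a bounded 0 to 7 count. Choose one form:

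1. a repeated-measures comparison over T1 to T3, which keeps the longitudinal objective and the stated sizing; or
2. modules completed by T1, with Sample Size restating power as about 92% at 223 per arm (81% at 167), below the planned 95%.

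State also how an absent usage record is handled. The app works offline and uploads later, so a missing record may be unsynchronised use and not zero use.

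Make log-ins, time in the app and any other time points supportive. Change Trial Design to co-primary, in line with the objectives and Sample Size.

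If the sponsor intends the aim to be exploratory, leave the analysis descriptive, change Trial Objectives and Purpose and Sample Size accordingly, and re-justify 669.

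Separately, the end date for new posts and articles in Trial Intervention and the one implied in Types of Safety and Monitoring must be reconciled.

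The cost is wording. No extra data or participants are needed; option 2 gives up some planned power.
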